### Sample size and analyses

Participants in this phase of the study will be naïve volunteers age-matched to typical patients with the condition discussed in the DA. Based on previous experience and the usability testing literature [93], four to five iterations of five to six participants each will be sufficient to meet the usability goals described above (*i.e.*, twenty to thirty participants will be required).

### Objective Four: prospective observational study

Objective four will compare the experiences of people using consent forms and DAs to assist hypothetical decisions about trial participation. This objective will consist of a prospective observational study designed to collect both qualitative and quantitative data relevant to whether this approach warrants further evaluation with a pilot RCT.

Participants will be naïve individuals who meet the inclusion criteria of the target study, and thus could have been approached to participate in the original study. However, those who actually were approached to participate in the target study, regardless of their decision to participate, will be excluded from our study. In addition to the type of decision tool (consent form, DA), the two consent forms that were subjected to user testing from objective three will be the focus of this study. Participants will be eligible for our study if they speak English, are over 18 years of age, and meet the inclusion criteria of one of the target studies.

Potential participants that meet one of the two sets of inclusion criteria will be approached to enrol in our study (*i.e.*, non-random allocation to target study), and standard consent will be obtained. Participants will work through one of the two decision support tools. Data will first be collected on consent forms, then later for DAs. We have chosen this approach for two reasons. First, by collecting data for consent forms initially, we will not need to wait until the end of DA user testing to begin data collection for objective four. Participants may need to fit strict inclusion criteria for the relevant studies chosen for objective four; this approach adds flexibility to our timeline. Second, we will incorporate information gleaned from the consent form participants (particularly their qualitative responses) to further improve the DA. This approach sacrifices the experimental rigour of an RCT, but adds a richness of qualitative and quantitative data that is most likely to result in both a tool that maximally improves the informed consent process, and in a better understanding of what outcomes are affected by the newer decision support tool.

After working through the decision support tool, participants will complete a paper-based questionnaire. This questionnaire will include validated measures of constructs related to decision quality, as well as qualitative questions about their impressions of recruitment process and materials. Quantitative outcomes measured will include decisional conflict [94], memory for key aspects of the decision, knowledge of the probabilities of different outcomes, values associated with different outcomes for comparison with the participation choice, and participation choice. We will also measure satisfaction with the decision support materials, satisfaction with the informed consent process [49], and anticipated regret of key negative outcomes. In addition, participants will be asked to make a hypothetical decision about whether or not they would participate in the target trial (yes, no, unsure). Of note, participants will not have access to the decision support materials when completing the questionnaire. At the end of the session, participants will be provided with a debriefing form, explaining the purpose of the study and how their data will contribute to towards improving the consent process. The entire session will take 45 to 60 minutes, for which participants will be offered $20 as a token of appreciation and to cover any attendant costs.

### Sample size and analyses

The sample size calculation was based on detecting differences on the continuous decisional conflict scale [43]. The authors selected this scale as the primary outcome for this analysis because it is considered a key correlate of good decision quality and has been well validated in the context of many treatment decisions. Sample size calculations were carried out by simulation using the AOV function of R statistical software [95]. We conducted a simulation with 50,000 iterations, detecting a 10% difference on a continuous outcome. Results of the simulation showed that a sample size of 30 individuals per group, or 120 in total, yields a proportion of rejecting the null when it is true of 0.048 (*i.e.*, alpha level is approximately 0.05), while the proportion of incorrectly accepting the null hypothesis is less than 0.01 (*i.e.*, power is greater than 0.99).

Analyses for this study will consist of linear (for continuous outcomes) and logistic regressions, with type of decision support (consent form/DA), target study, and their interaction predicting the different outcomes. For example, when predicting decisional conflict, a significant effect of type of decision support will indicate whether those making decisions on the basis of consent form and DA differ in terms of how unsure they remain about the decision. Similarly, a significant effect of target study will demonstrate whether satisfaction was higher for one condition regardless of type of decision support, and their interaction will show whether the two effects are independent. The collected demographic characteristics of respondents (*e.g.*, age, sex) will also be included as covariates.

Hypotheses for this objective were principally derived from literature on the effects of DAs on treatment decisions, *i.e.*, that they improve the quality of decision-making. The authors hypothesize that using a DA will result in: reduced indecision and decisional conflict [39,40,45,61,62]; improved memory for key aspects of the decision [64,96]; improved knowledge of key outcome probabilities [40]; and a higher correlation between self-identified important outcomes and the selected treatment choice [40,97]. Literature has shown that DAs can affect behavioural outcomes, such as increased use of underused treatments [51,52], and that that confusion arising from consent forms may contribute to non-participation [48]. As a result, we further hypothesize that DAs may increase participation in trials where risk/benefit ratios are favourable.

Finally, we will collect and analyze the number and content of questions that potential participants ask after working through the decision support materials. These post-consent form discussions will not only serve to make the consent process more representative of real world recommended practice [48], they will also serve as a valuable data collection opportunity. The DA will explicitly ask people to record any unanswered questions about the associated trial, while encouraging systematic thinking about the various possible outcomes. As a result, we expect that more questions, and more detailed questions, will stem from those working through the DA as opposed to the consent form. The enrolment rates of the sample consent participants will be compared to the reported trial enrolment rates, to estimate how closely hypothetical recruitment mimics real life situations.

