We will develop DAs for two target studies from the set of trials assessed in objective one. Although UCD testing is labour intensive, developing two DAs instead of one will help identify which issues can be generalized and which issues are idiosyncratic to specific studies. The choice of which two trials to focus on will be determined by two main criteria. First, studies whose inclusion criteria are extremely strict, or where the relevant population does not exist locally, will be avoided to allow enough participants to be recruited for objective four. Second, if there is significant variation in the extent to which consent forms adhere to standards (objective one, hypothesis one), the investigator group will choose one trial that meets relatively few criteria and one that meets more. This selection process will allow us in objective four to study whether a DA only affords a benefit over poorly designed consent forms. Note that analysis for this objective will be exploratory in nature, since any differences in the number of criteria met will be confounded with clinical condition.

Risk information will be consistent for both consent forms and DAs (*i.e.*, the DA will not introduce any new risk information). While both the DA literature and the IPDAS criteria recommend providing specific numbers associated with the risks of different outcomes, such specific outcome probabilities are often not available for clinical trials. Therefore, for the purposes of this project, specific outcome probabilities will not be included in the DA if they are not provided in the associated consent form. Instead, the DA will contain standardized descriptors, such as those recommended by the National Cancer Institute of Canada (*e.g.*, common = > 200 per 1000, very rare =< 1 per 1000) [90].

Data collection for this objective will consist of two phases of qualitative UCD testing: expert testing and user testing. Phase one will involve experts (three DA experts and three content areas, drawn from the investigator team and colleagues) working through the DA to ensure that all information relevant to the decision is present. They will examine the DA to ensure formatting conforms to basic principles or 'heuristics' of good design (heuristic evaluation [91]). These experts will also identify potential stumbling blocks in the material by working through the entire tool; this technique is referred to as a 'cognitive walkthrough' [92].

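### Objective Four reads a significant target-study term as holding whichever tool was used, but with the interaction in the model that term shows at most an average over the two tools (minor)

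*Protocol article*

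**What the plan says.** In the Protocol article, Objective Four, Sample size and analyses, the outcomes are analysed by linear and logistic regression "with type of decision support (consent form/DA), target study, and their interaction predicting the different outcomes", with demographic covariates. The text then explains how each term will be read:

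- Tool: "a significant effect of type of decision support will indicate whether those making decisions on the basis of consent form and DA differ".
- Target study: "a significant effect of target study will demonstrate whether satisfaction was higher for one condition regardless of type of decision support".
- Interaction: "their interaction will show whether the two effects are independent".

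The design is "a sample size of 30 individuals per group, or 120 in total", that is, four cells of 30. On the calculation behind it, the section says: "Sample size calculations were carried out by simulation using the AOV function of R statistical software". The article does not state the coding of the factors. It also does not say that the interaction is examined before the main effects are interpreted.

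Objective Three says that, if consent forms vary enough in how far they meet the standards, one target trial meeting few criteria and one meeting more will be chosen. Objective Four could then "study whether a DA only affords a benefit over poorly designed consent forms". The same paragraph calls that analysis exploratory and confounded with clinical condition.

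**The concern.** To say that one study scores higher whichever tool was used is to say that the difference exists under the consent form and also under the DA. A single coefficient from a model containing the interaction does not test that. With centred or ANOVA-type coding, the target-study term tests whether the mean of the two within-tool differences is zero. A large difference under one tool and none under the other gives a non-zero mean, so the test can properly reject while the stated conclusion is false.

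The sentence goes on to give the question of independence to the interaction. That helps only if the interaction test would usually detect the dependence, and at 30 per cell it often would not. At stake is a published statement that a difference between target studies holds under both tools when it was present under only one. The possible pairing of a weak with a stronger consent form makes dependence between tool and study a pattern that the authors themselves have in mind.

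**Working it through.** **Inputs.** From Objective Four, Sample size and analyses: four cells, 30 per cell, 120 in total, and alpha of about 0.05 (taken as two-sided). The SD is not stated, so effects are expressed in SD units over an assumed range of 0.5 to 1.0. Outcomes are taken as normal, cells as balanced and covariates are ignored.

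**The plan's own figure.** The stated power is above 0.99 for "detecting a 10% difference on a continuous outcome". The term tested is not named. For a main effect (60 v 60), 99% power needs a standardised difference of (1.960 + 2.326) × √(2/60) = 0.78. If the 10% means 10 points on a 0–100 scale (an assumption), the SD must be no more than 10/0.7826 = 12.8. Power would be 0.992 at SD 12.5, 0.955 at SD 15 and 0.782 at SD 20. Without an SD the stated power can be neither confirmed nor refuted, and the point here does not depend on it.

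**Standard errors, in SD units, n = 30 per cell.**

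- Study effect averaged over tools: √(1/30) = 0.183
- Study effect within one tool: √(2/30) = 0.258
- Interaction (difference of the two within-tool effects): √(4/30) = 0.365, twice the first

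**Study difference d under one tool, none under the other.** The averaged effect is d/2 and the interaction is d in absolute size. The two expected z values coincide: (d/2)/0.183 = d/0.365. The averaged term is therefore as likely to be significant as the interaction that should warn against it. In a balanced layout the two contrasts are uncorrelated. If p is their common power, the chance that the averaged term is significant and the interaction is not is about p(1 − p), which cannot exceed 25%.

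By normal approximation, p = Φ(d/0.365 − 1.96):

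- d = 0.5: p = 0.28, p(1 − p) = 0.20
- d = 1.0: p = 0.78, p(1 − p) = 0.17

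Simulation of 50,000 data sets per row (pooled variance, t test on 116 df), with the difference under the consent form only:

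| d (SD) | Averaged term significant | Interaction significant | Averaged significant, interaction not |
|---|---|---|---|
| 0.5 | 27% | 28% | 19% |
| 0.725 | 50% | 51% | 25% |
| 0.8 | 59% | 59% | 24% |
| 1.0 | 78% | 78% | 17% |

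Placing the difference under the DA only changes these by no more than one percentage point. With no effects at all the averaged term rejects in 5.0%, so the test is valid for its own null hypothesis; only the reading of it is wrong.

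**Opposite directions.** With +1.0 SD under one tool and −0.3 SD under the other, the averaged term is significant in 48%. The interaction is significant in 94%, and the unwarned case falls to about 3%. The interaction test thus protects well against a marked reversal, but poorly against a one-tool effect.

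**Interaction power on the assumed point scale.** For a 10-point interaction it is 0.78, 0.59, 0.45 and 0.28 at SD 10, 12.5, 15 and 20.

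**The case against.** The strongest reply is that the sentence should be read whole. In factorial work, regardless of is common shorthand for collapsed over the other factor, and the next clause gives dependence to the interaction. AOV in the sample-size simulation points to averaged main effects. The affected sentence concerns satisfaction and target study, not the primary comparison of tools on decisional conflict. Target study is allocated non-randomly, Objective Three labels the form-quality comparison exploratory, and the Limitations disclaim strong claims about DAs versus consent forms.

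Most of this stands, and it limits the point to a minor one. It does not remove it. The text says the term will demonstrate the result, no order of interpretation is set, and the table shows that a non-significant interaction is weak reassurance at this size.

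A reader might infer two stronger points that the document does not support:

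- **That the tool effect is misread in the same way.** It is not. The tool sentence claims only that users of the two tools differ, which an averaged contrast supports.
- **That the regressions will use 0/1 coding, so that each main-effect term describes a single reference cell.** Under that coding the target-study term would be significant in about 49% to 97% of data sets if the difference lay in the reference tool, and in about 5% if it lay in the other. The tool coefficient would likewise be the DA effect in one study only. But no coding is stated, an article may leave that detail to the full plan, and R is cited only for the simulation. This is a risk to close, not an error in the document.

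**Conclusion.** The point holds for the target-study sentence. The term supports at most a difference averaged over the two tools. When the studies differ under one tool only, by 0.5 to 1.0 SD, the stated conclusion would be drawn falsely in about 27% to 78% of data sets on the main effect alone. It would be drawn falsely in about 17% to 25% even if a non-significant interaction were also required. These figures rest on the assumed effect range, a normal outcome, balanced cells and no covariates. The logistic models were not simulated, but the logic of the contrast is the same on the log-odds scale. The model is appropriate, and the defect lies in the stated interpretation. Severity is minor.

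**What to change.** In Objective Four, Sample size and analyses:

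1. Describe a significant target-study effect as a difference on average over the two tools. Claim a difference under both tools only if each within-tool difference is itself shown.
2. State that the tool effect is the DA-minus-consent-form contrast averaged equally over the two target studies (both factors coded −1/2, +1/2, in the linear and the logistic models). This agrees with the AOV simulation and closes the coding question.
3. Report the DA effect within each target study, and the interaction estimate, with 95% confidence intervals. Label them exploratory, as Objective Three already does for the form-quality comparison.
4. Say that a non-significant interaction will not be taken as showing that the effects are independent.

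The cost is a few sentences and a coding choice, with no added participants or data. The downside is that a claim of a difference under both tools becomes harder to make: each within-tool contrast rests on 30 v 30, with a standard error of 0.258 SD against 0.183 SD for the average.

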Third, objectives three and four will make use of hypothetical decision-makers rather than actual patients making real world decisions. This characteristic is common in the literature, but has been argued to adversely affect study generalizability [48]. However, increasing evidence shows that decision-making based on hypothetical, written scenarios is highly correlated with real world decisions [100,101]. This study is designed to determine whether incorporating DAs into real informed consent decisions is worthwhile; as such, we felt that it would be inappropriate to use actual patients until it is known whether DAs are at least as effective as standard practice in assisting decision-making. However, it may be that in this context, hypothetical decisions are not predictive of actual decisions. This issue will be addressed by examining the calibration of hypothetical enrolment rates from objective four with true enrolment rates collected in objective one. Determining the usefulness of DAs for true participation decisions will be the subject of another study.

Fourth, objective four will compare online DAs to existing, paper-based consent forms, which are still the current norm for most clinical trials. This comparison leaves open the possibility that any observed variation could stem from the difference in media (paper-based versus online) rather than differences in the decision support tool itself (consent form versus DA). However, a recent systematic review of interventions designed to improve informed consent documents showed that presenting the information online is not enough to ensure better understanding, and a meta analysis of all multimedia manipulations showed a null effect on consent form knowledge [48]. As a result, we expect that any response differences between the two types of decision material will be primarily due to variations in the support framework, rather than any implicit advantage in the display medium.

Fifth, blinding, allocation concealment and randomization for objective four are impossible or impractical, and thus strong claims about the relative benefits of DAs versus consent forms cannot be made. The next step in this research program will address this issue by comparing the performance of DAs and consent forms in the context of a real world RCT.

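### The calibration of hypothetical against real enrolment counts only people who had already consented to a research study, so it cannot separate selection from hypothetical-decision error

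*Protocol article*

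**What the plan says.** All references are to the protocol article.

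- **Entry (Objective Four: prospective observational study).** "Potential participants that meet one of the two sets of inclusion criteria will be approached to enrol in our study", and "standard consent will be obtained". Only then do participants work through a consent form or decision aid and say whether they would join the target trial (yes, no or unsure). Anyone who had been approached for the target trial itself is excluded.
- **Comparison (Objective Four, Sample size and analyses).** "The enrolment rates of the sample consent participants will be compared to the reported trial enrolment rates", with the aim "to estimate how closely hypothetical recruitment mimics real life situations".
- **Source of the real rate (Objective One: comparing consent forms to standards).** Principal investigators of the sampled trials are asked about enrolment in their trials overall. The text does not say whether the denominator is people screened, eligible or approached, or something else.
- **Use of the comparison (Limitations, third item).** After conceding that hypothetical decisions may not predict actual ones here, the text says: "This issue will be addressed by examining the calibration of hypothetical enrolment rates from objective four with true enrolment rates collected in objective one".

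No count of people who decline objective four is described. Selection through prior research consent is not among the listed limitations.

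**The concern.** The two rates describe differently selected people. A person who declines objective four never gives a hypothetical decision and so leaves both the numerator and the denominator of the hypothetical rate. Nothing in the document imposes a matching step on the people behind the original trials' rates.

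The gap between the two rates therefore has at least two sources: how people answer a hypothetical question, and who was available to answer it. The plan attributes the gap to the first source alone. If the people who agree to objective four are also readier to join trials, a positive gap can appear with perfectly realistic answers. A match can then conceal answers that understate real willingness. What is at stake is how the calibration can be read, and through it the response to the third limitation.

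**Working it through.** The document gives no figure for this comparison, so there is none to reproduce. The steps below show when the mismatch matters and how large it could be.

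**Inputs**

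- *c*, share of eligible people approached who consent to objective four: not given; assumed 50% to 90%.
- *p*, share of participants who say they would join the target trial: not given.
- *q*, share of decliners who would have said they would join: never observed under the plan.
- *t*, the rate among all people approached: not given; assumed 30%.
- ρ, latent correlation between willingness to join objective four and willingness to join the target trial: not given; assumed 0 to 0.7.
- Group size: 30 per group, 120 in total (Objective Four, Sample size and analyses). With two tools and two target studies, that is 30 consent-form users per target study and 60 over both.

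**Step 1: the identity.** The rate among all people approached is

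*t* = *c* × *p* + (1 − *c*) × *q*,

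so the selection error in using *p* for *t* is *p* − *t* = (1 − *c*)(*p* − *q*). It is zero only if everyone consents or if decliners would answer as participants do. Its sign is the sign of *p* − *q*.

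**Step 2: bounds without a model.** As *q* runs from 0 to 1, *t* lies between *c* × *p* and *c* × *p* + (1 − *c*). With *p* = 70% (assumed):

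- *c* = 60%: 0.6 × 0.7 = 42%, up to 42% + 40% = 82%.
- *c* = 80%: 0.8 × 0.7 = 56%, up to 56% + 20% = 76%.

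Both intervals contain 70%, so on bounds alone the direction is open.

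**Step 3: size under a positive correlation.** Assume bivariate normal latent willingness and fully realistic hypothetical answers. Then *p* = Φ₂(z_t, z_c; ρ) / *c*, where z_t and z_c are the normal quantiles of *t* and *c*. The ceiling is min(1, *t*/*c*). With *t* = 30%:

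| *c* | ρ = 0 | ρ = 0.3 | ρ = 0.5 | ρ = 0.7 | ceiling |
|---|---|---|---|---|---|
| 50% | 30.0% | 38.4% | 44.3% | 50.8% | 60.0% |
| 70% | 30.0% | 35.0% | 38.1% | 41.0% | 42.9% |
| 90% | 30.0% | 31.8% | 32.7% | 33.2% | 33.3% |

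For ρ from 0.3 to 0.7 the inflation runs from 31.8 − 30 = 1.8 points to 50.8 − 30 = 20.8 points, or roughly 2 to 21.

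**Step 4: what a match or a gap would mean.** Take *c* = 70% and ρ = 0.5. Realistic answers give 38.1% against a true 30%, a gap of 8.1 points that has nothing to do with the decision being hypothetical. If answers instead understated willingness by 8.1 points, the two rates would coincide and the check would look well calibrated.

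**Step 5: sampling error for scale.** The 95% half-width of a rate near 30% is 1.96 × √(0.3 × 0.7 / *n*): 16.4 points at *n* = 30 and 11.6 points at *n* = 60. Selection error can be smaller or larger than this, but it does not shrink as *n* grows.

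**The case against.** **The comparator is an inference.** The document does not define the original trials' enrolment rate. It might be accrual against a target, in which case the rates would fail to match for another reason. An article may also leave such a definition to a fuller protocol. This stands as a limit on what can be asserted. However, no stated feature of that rate requires prior consent to a separate study, whereas objective four's procedure does. The fault lies in the comparison as stated, not in a missing definition.

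**The direction is not established.** A reader might infer that the check is wrong in a predictable direction. The document does not support this: Step 2 leaves the sign open, and nothing in the text shows that people who decline a 45 to 60 minute session with a $20 payment would also decline a trial. Upward bias is likely only given a positive correlation, which is an assumption.

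**The size may be modest.** At *c* = 70% and ρ of 0.3 to 0.5 the inflation is about 5 to 8 points, below the sampling half-widths in Step 5. That is correct for that scenario. At *c* = 50% and ρ = 0.7 it is about 21 points, above both.

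**The check carries limited weight.** A reader might take it as the plan's only safeguard against unrealistic hypothetical answers. It is not: Limitations also cites outside evidence that hypothetical and real decisions are correlated, and leaves real participation decisions to another study. No decision rule hangs on the check.

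**A ceiling on the decision-aid effect.** A reader might infer that the filter raises the consent-form rate so far that little room remains for the hypothesised increase. The document gives no baseline participation rate to support this, the filter applies to both tools, and in the 30% illustration the filtered rates stay at or below 51%.

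**Conclusion.** The concern holds in a limited form. As written, the calibration compares a rate among people who had already agreed to take part in research with a rate for which no such agreement is required. It therefore mixes selection with hypothetical-decision error, and neither a match nor a gap can be read as showing how well hypothetical decisions mimic real ones.

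The inflation is probable if the two kinds of willingness are positively correlated, and absent if they are unrelated or everyone consents. The range of roughly 2 to 21 points rests on the assumed inputs of Step 3 and is an illustration, not an estimate for this study. Only a secondary check is affected; decisional conflict, the primary outcome, is not. Because Limitations offers the check in answer to a named weakness, and the repair costs almost nothing, the change is worth making.

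**What to change.** 1. Log every eligible person approached for objective four and whether they agreed. Start with the consent-form participants, who are recruited first, since uncounted decliners may not be recoverable later.
2. Ask the original investigators for the number enrolled over the number eligible and approached, so that the denominators correspond.
3. Report the hypothetical rate among participants (*p*) with both bounds for all people approached: *c* × *p* if every decliner would say no, and *c* × *p* + 1 − *c* if every decliner would say yes.
4. Claim miscalibration only if the real rate lies outside those bounds, allowing for sampling error. Otherwise state that selection by prior research consent could explain the gap or the match.

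In the Step 4 example with realistic answers, the bounds are 0.7 × 38.1% = 26.7% and 26.7% + 30% = 56.7%. They contain the true 30%, so the rule correctly makes no claim of miscalibration. Requiring the participant rate to agree with the lower bound would not serve as a rule: for any non-zero *p*, *c* × *p* equals *p* only when everyone consents.

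The cost is an approach log, one more specific request to investigators and extra rows in one table. The downside is that the calibration becomes a range of width 1 − *c*: 20 points if 80% consent and 40 points if 60% do. With low consent it may be uninformative, and the report should then say so.
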